**1.5 Study Objectives.**

Endpoint definitions.

PBD:

≥ 25% progression in size of existing osteolytic lesions (a total growth of at least 10 mm is required in the longest dimension) or vertebral fractures, new osteolytic lesions (at least 10 mm in the longest dimension) or fractures, spontaneous factures, new vertebral compression, new osteolytic lesions needing irradiation therapy or surgery, hypercalcaemia caused by the myeloma (S-Ca-ion > 1,40 mmol/L or in case S-Ca-ion is not measured: S-Calcium adjusted for S-albumin > 2,75 mmol/L), measured in at least two consecutive blood samples.

PBD can be diagnosed on either conventional radiography or low-dose CT. The development however must be defined by comparing the same modality over time. The modality used at the time of randomisation (year 2) will be used as baseline value.

sPBD:

Spontaneous factures, new vertebral compression, new osteolytic lesions needing irradiation therapy or surgery, hypercalcaemia caused by the myeloma (S-Ca-ion > 1,40 mmol/L or in case S-Ca-ion is not measured S-Calcium adjusted for S-albumin > 2,75 mmol/L), measured in at least two consecutive blood samples).

sPBD can be diagnosed on either conventional radiography or low-dose CT. The development however must be defined by comparing the same modality over time. The modality used at the time of randomisation (year 2) will be used as baseline value.

Bone healing:

≥ 25% reduction in the size of osteolytic lesions (a reduction of at least 10 mm in the longest dimension is required), increased sclerosis in the edge of existing lesions, or healing of existing lesions. Bone healing can be diagnosed on either conventional radiography or low-dose CT. The development however must be defined by comparing the same modality over time.

The modality used at the time of randomisation (year 2) will be used as baseline value.

BON:

To diagnose BON the following criteria must be fulfilled

1: Current or previous treatment with a bisphosphonate AND

2: Exposed, necrotic bone in the maxillofacial region that has persisted for more that 8 weeks AND

3: No history of radiation therapy to the jaws [[29](#_ENREF_29)]

No bone disease / Bone disease:

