Any radiological signs of bone disease including osteolysis (at least 10 mm), osteopenia, halisteresis, fractures including vertebral compression fractures (these findings are not necessarily equal to a Myeloma Defining Bone Disease Event; which is defined according to the International Myeloma Working Group Consensus Statement Paris 2011). No bone disease / Bone disease can be diagnosed on either conventional radiography or low-dose CT

QoL:

Quality of Life is evaluated using the European Organization for Research and Treatment of Cancer Quality of Life Questionnaire-Core 30 (EORTC QLQ-C30, version 3.0, together with the MY20 multiple myeloma specific supplement.

Primary Endpoint:

To compare the time to PBD from year 2 to year 4 in patients treated with monthly zoledronic acid in two consecutive years compared to patients treated with monthly zoledronic acid in four consecutive years.

Secondary Endpoints:

To compare the incidence of PBD from year 2 to year 4 in patients treated with monthly zoledronic acid in two consecutive years compared to patients treated with monthly zoledronic acid in four consecutive years.

To compare the incidence of sPBD from year 2 to year 4 in patients treated with monthly zoledronic acid in two consecutive years compared to patients treated with monthly zoledronic acid in four consecutive years.

To compare the incidence of bone healing from year 2 to year 4 in patients treated with monthly zoledronic acid in two consecutive years compared to patients treated with monthly zoledronic acid in four consecutive years.

To compare the overall survival from year 2 to year 4 in patients treated with monthly zoledronic acid in two consecutive years compared to patients treated with monthly zoledronic acid in four consecutive years.

To compare the incidence of BON from year 2 to year 4 in patients treated with monthly zoledronic acid in two consecutive years compared to patients treated with monthly zoledronic acid in four consecutive years.

To compare the development in QoL from year 2 to year 4 in patients treated with monthly zoledronic acid in two consecutive years compared to patients treated with monthly zoledronic acid in four consecutive years.

To compare the development in the bone markers CTX-I, PINP, bALP, and TRAP5b from year 2 to year 4 in the patients groups randomised to receive two or four years of treatment with zoledronic acid

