-The patient should have received at least 12 infusions with zoledronic acid in the previous two years period. If a patient has received less than 12 infusions in the previous two years he / she it not eligible for randomisation and should leave the study.

Patients who fail to be included in the study will be treated according to the local standards. Patients who will be excluded from the study because they fail to meet the criteria for randomisation (at year two) will likewise be treated according to the local standards. Radiological data from these patients will still be used to evaluate secondary endpoints in the study. No additional protocol related follow-up is planned once the patients leaves the protocol either timely or untimely. Future treatment will be decided by the local hospital and the patient.

Amendment: Patients may be included when they have received two years of zoledronic acid treatment outside clinical trials. They will proceed directly to randomisation

Inclusion criteria (amendment)

- Earlier diagnosed with symptomatic Multiple Myeloma according to the IMWG criteria, regardless of bone disease status

-Signed Informed Consent

-Age ≥ 18 years

-Remaining life expectancy ≥ 1 years

-Received 23-25 monthly infusions with zoledronic acid

-Any concurrent anti-myeloma treatment are allowed

Exclusion criteria (amendment) :

-Severely reduced renal function (creatinine clearance <30 mL/min despite fluid replacement)

-Known concurrent malignancy, excluding skin cancer

-Known hypersensitivity to zoledronic acid

-Pregnant or lactating women

-Women of childbearing potential or men engaging in sexual activity with a woman of childbearing potential who refuse to use contraception (safe methods of contraception are considered to be: combined (estrogen and progestogen containing) hormonal contraception associated with inhibition of ovulation, progestogen-only hormonal contraception associated with inhibition of ovulation, intrauterine device (IUD), intrauterine hormone-releasing system ( IUS) bilateral tubal occlusion, vasectomy, and sexual abstinence. Contraception must be used until 56 days after the last infusion).

- Progressive bone disease diagnosed using bone imaging, less than or equal to three month prior to the randomization

- Developed BON during earlier zoledronic acid treatment

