Fasting serum bone markers will be collected bi–annually. All time-points can be moved +/- 2 weeks.

Measurements of creatinine and calcium may be conducted up till 2 weeks before the visit

QoL questionnaire QLQ-C30 and MY20 will be used bi-annularly. All time-points can be moved +/- 2 weeks.

Infusion with zoledronic acid should be given ever 4^th^ week (+/- 1 week). Infusion can be delayed for up to 2 months e.g. due to temporarily impaired renal function (meaning a three month pause between two infusion is allowed). If infusions cannot be given within this time period the patient will be excluded from the study. If infusions are delayed for a significant period, it is the time passed and not the number of infusions that is relevant as to when stratification occurs.

Randomisation:

At year 2 patients will be randomised to A) stop treatment with zoledronic acid or to B) continue treatment with monthly infusions of zoledronic acid for another 2 years period (4 years in total). Randomisation is allowed to be moved -1months/+2months. The randomisation procedure will be stratified according to previous autologous stem cell treatment, presence or absence of bone disease at diagnosis, and previous treatment with bortezomib. Randomisation will take place at The Hematological Research Unit, Odense University Hospital, Denmark. For further details see appendix 6 (SOP for randomisation).

Planned visits, year 2-4:

Bone imaging will be conducted after 2½ years, after 3 years, after 3½ years, and after 4 years. All time-points can be moved +/- 1 month. In case of myeloma relapse requiring active treatment, new bone imaging should be conducted within a one-month time frame of initiation of new anti-myeloma treatment. If bone imaging has been conducted as part of relapse evaluation no less than three month prior to routine bone imaging time point,no new bone imaging need to be conducted. If any bone imaging, conducted from year 2 to 4, reveals PBD in patients not receiving zoledronic acid and the treating physician find it necessary to reinitiate treatment with zoledronic acid, the patient will be excluded from the study. In that case, fasting serum bone markers should be measured prior to re-initiation of zoledronic acid treatment. If bone imaging, conducted as part of a myeloma relapse evaluation in patients not receiving zoledronic acid, results in “no PBD”, treatment with zoledronic acid should *not* be re-initiated.

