**1.12 Withdrawal from the Study.**

In accordance with the current revision of the Declaration of Helsinki and applicable regulations, a

patient has the right to withdraw from the study at any time for any reason without prejudice to

his/her future medical care by the physician or at the institution.

Patients may be excluded from study in case of:

-significant protocol violation or non-compliance

-refusal of the patient to continue treatment and observations; withdrawal of consent

-if the investigator believes that for safety reasons (e.g., adverse events), it is in the best interest of the subject to stop treatment.

-if the patient due to renal failure is unable to receive zoledronic acid in two consecutive months (infusion can be delayed for up to three months). In case of tooth extraction, a delay of up to four months is allowed.

-if the patient due to BON stops treatment with zoledronic acid.

-if patients in the control arm experience progressive bone disease and the treating physician find it in the best interest of the patient to reinitiate treatment with zoledronic acid.

-if the subject becomes pregnant

-death

Patients excluded from the study will be followed for 30 days by the local hospital to insure registration of late occurring AE, SAE, SAR and SUSARs

The date and the reason for withdrawal status should be stated in the case report form. If the patient withdraws his or / her consent no further investigations will be conducted. If the patient is excluded for other reasons and it poses no risk for the patient fasting serum bone marker should be measured upon withdrawal, and bone imaging should be conducted no less than one month after withdrawal from the study. Data collected from the patient up until the time of withdrawal will if possible be used in the final evaluation of the study result unless the patient states it otherwise.

As stated in section 1.13, 286 patients need to be randomised to achieve enough power in the study. Patients will be included until this number is reached

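### Exclusion after randomisation ends outcome follow-up, and its triggers differ by arm, so survival, later sPBD and later BON to year 4 face arm-dependent informative censoring

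*Protocol*

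**What the plan says.** **Follow-up after exit.** Section 1.6: "No additional protocol related follow-up is planned once the patients leaves the protocol either timely or untimely". Section 1.12: "Patients excluded from the study will be followed for 30 days by the local hospital", for late adverse events. Unless consent is withdrawn, section 1.12 also asks for a marker sample at withdrawal and says "bone imaging should be conducted no less than one month after withdrawal from the study". On use of the data: "Data collected from the patient up until the time of withdrawal will if possible be used in the final evaluation".

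**Exit in arm A (observation).** Under section 1.7, if imaging between years 2 and 4 shows PBD in a patient off the drug and "the treating physician find it necessary to reinitiate treatment with zoledronic acid, the patient will be excluded from the study". Section 1.12 repeats the rule for the control arm. No rule removes an arm B patient because of PBD.

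**Exit in arm B (continued treatment).** Sections 1.7, 1.8 and 1.12 exclude patients who stop the drug because of BON, or whose infusions are interrupted beyond the permitted gap, for example by renal failure.

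**Endpoints.** Section 1.5 lists, among others, "To compare the overall survival from year 2 to year 4 in patients treated with monthly zoledronic acid in two consecutive years" against four years, and the incidence of sPBD and BON over the same period. BON requires "Exposed, necrotic bone in the maxillofacial region that has persisted for more that 8 weeks".

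**The concern.** Three secondary endpoints run to year 4, but observation stops at exit. Exit is tied to the outcome in arm A (PBD) and to toxicity or tolerance in arm B. PBD is wider than sPBD, and section 1.14 says imaging is meant to find it before symptoms. An arm A patient can therefore leave with radiographic PBD before a fracture or death, while an arm B patient with the same finding stays and is counted. An arm B patient who leaves for renal failure or an infusion gap is lost to later PBD, sPBD, BON and death.

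Censoring of this kind breaks the assumption behind the Kaplan-Meier method. An analysis plan cannot repair it, because the data are never collected. It matters because section 1.4 cites a survival gain in the rationale, and section 1.20 asks the steering committee to weigh PBD benefit against BON.

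**Working it through.** **1. Reproducing the plan's sample size (section 1.13).** Inputs: 7.5% per year on drug; ratio 0.5, so 15% off drug; one-sided 0.05; 80% power; 2 years.
- Events (Freedman): [(1 + 0.5)/(1 − 0.5)]² × (1.645 + 0.842)² = 9 × 6.18 ≈ 56.
- Two-year risks, exponential: 1 − exp(−0.15) = 13.9% in arm B and 1 − exp(−0.30) = 25.9% in arm A.
- Per arm: 56/0.398 ≈ 141, against 143 stated. Inclusion: 286/0.8 = 357.5, so 358 as stated. The rates are read correctly.

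**2. How many arm A patients could leave through PBD.**
- 143 × 25.9% = 37 with PBD within two years. In arm B, 143 × 13.9% = 20, and none leaves by this route.
- Allowing for deaths before PBD at an assumed 10% per year: 143 × (0.15/0.25) × (1 − exp(−0.50)) = 34.
- The share who restart is not stated. At 25/50/75/100% of the 37, about 9/19/28/37 leave.
- Section 1.13 expects only 32 PBD cases in both arms together. That equals 143 × (0.075 + 0.15) = 32.2, one year's worth. On that figure arm A has 143 × 0.15 ≈ 21 cases, and about 5 to 21 leave.

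**3. Effect on survival (illustration; the protocol gives no hazards).** Assume a death hazard d = 0.10 per year before PBD and k × d after it, PBD at 15% (A) and 7.5% (B) per year, and no arm B exits. The death rate observed over two years is d × [1 + (k − 1) × s], where s is the share of observed person-time spent after PBD.

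| | s, k = 2 | rate | s, k = 3 | rate |
|---|---|---|---|---|
| Arm B, all followed | 6.5% | 0.1065 | 6.1% | 0.1123 |
| Arm A, all followed | 12.4% | 0.1124 | 11.8% | 0.1235 |
| Arm A, all leave at PBD onset | 0 | 0.1000 | 0 | 0.1000 |
| Arm A, half leave, six-monthly detection | 8.2% | 0.1082 | 7.8% | 0.1156 |

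A/B ratios:
- True: 0.1124/0.1065 = 1.06 and 0.1235/0.1123 = 1.10.
- All leave at onset: 0.1000/0.1065 = 0.94 and 0.1000/0.1123 = 0.89.
- Half leave, six-monthly detection: 0.1082/0.1065 = 1.02 and 0.1156/0.1123 = 1.03.
- If k = 1, the rate is d in every row and there is no bias.

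Six-monthly detection follows the visit schedule in section 1.7. Section 1.8 says imaging is every 3 months, and the two passages must be reconciled.

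**4. Arm B exits.** The protocol gives no rate. At an assumed 5% to 15%, 143 × 0.05 to 143 × 0.15 = 7 to 21 patients leave.

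**5. BON timing.** Eight weeks is 56 days and follow-up after exit is 30. A lesion first noted in the last 26 days before exit cannot be watched for 8 weeks within that window. The same holds at the end of the study, where section 1.9 ends event registration 30 days after year 4 (observation arm) or after the last infusion (treatment arm).

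**The case against.** The strongest counter-arguments, and what remains of each:

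- **The sentence in section 1.6 concerns patients who were never randomised.** It does follow text about them. But a timely departure can only mean completing the study, so the wording covers every exit, and no later section restores outcome follow-up.
- **The loss is in both arms.** This stands. A reader might infer that outcomes go missing only in arm A and that the survival comparison must therefore favour stopping. The protocol does not support that. Arm B also loses patients unfollowed, and if those with renal failure die sooner, their loss favours continuing. The net direction is undetermined.
- **A large bias needs extreme assumptions.** This stands too. Observed ratios of 0.89 and 0.81 against a truth of 1.00 arise only with 15% PBD per year in both arms and every arm A case leaving at onset. Half leaving at six-monthly imaging gives 0.96 and 0.94, and the plan itself assumes 7.5% on drug.
- **BON and sPBD are partly captured.** Correct. BON that causes the exit is already recorded. Section 1.9.1 provides an end-of-study assessment, and care until the condition settles, after adverse-event exits. A first event that is symptomatic counts before the patient leaves. What is lost is sPBD after an earlier radiographic PBD, and BON arising after exit. A late lesion with documented earlier onset can still meet the 8-week criterion.
- **The primary endpoint is safe.** Only in part. PBD is the event itself, so leaving because of it does not bias time to first PBD. Arm B exits before PBD may.

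**Conclusion.** The point holds as arm-dependent informative censoring of overall survival, later sPBD and later BON, with a possible and unquantified effect on time to PBD through arm B exits. It does not hold as a one-sided loss with a known direction.

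On the plan's rates, up to 37 arm A patients (34 allowing for deaths, about 21 on the protocol's own 32 cases) could leave through PBD, reduced to the share who restart. The survival distortion ranges from none, if PBD does not affect mortality, to a modest true excess in arm A appearing as a deficit (1.06 and 1.10 seen as 0.94 and 0.89) in the extreme case. In the milder case the excess shrinks to 1.02 to 1.03. These figures rest on an assumed 10% yearly death hazard, a doubling or tripling after PBD, and arm B exits set aside.

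**What to change.** 1. **Section 1.6:** limit the no-follow-up sentence to patients who are not randomised. Add: *Every randomised patient who has not withdrawn consent is followed to year 4 for vital status, and for sPBD and BON from clinic records, whatever treatment is given.* The patient log in section 1.15 already links protocol numbers to civic registration numbers.
2. **Sections 1.7, 1.8 and 1.12, exits in years 2 to 4 only:** describe patients who leave for treatment-related reasons as off study treatment, not excluded from the study. Leave the exclusion rule for years 0 to 2 unchanged.
3. **Section 1.12:** reconcile the limit on data use at withdrawal with item 1, so that it applies only where consent is withdrawn.
4. **Section 1.13:** state that survival, sPBD and BON are analysed as randomised. The as-treated, per-protocol statement there, made under the primary endpoint, would otherwise leave the new data unused if carried over.
5. **BON:** record the outcome of any jaw lesion open at exit or at month 48 against the 8-week criterion.

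Cost: an amendment, register and record look-up, and less standardised sPBD ascertainment after exit, because routine imaging is not the scheduled same-modality imaging. For that reason the fix does not recover radiographic PBD after an arm B exit. No treatment decision changes.

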**1.6 Study Population.**

The study population comprises 358 patients with newly diagnosed symptomatic multiple myeloma. Patients with myeloma are in the Nordic countries treated in haematological clinics The patients will be recruited from participating haematological clinics within the NMSG. All patients will be invited to participate in the protocol if they fulfil the inclusion- and exclusion criteria´s. The patient will be informed of the protocol by the treating physician orally and receive written information in their own language concerning the protocol, according to the ICH-GCP guidelines. If possible, the patient will be encouraged to bring a family member to the information meeting. If needed, the patient will receive time for considerations before deciding if he/she wishes to participate in the protocol. If the patient decides not to participate in the protocol he/she will receive the clinics standard treatment.

Inclusion criteria:

-Symptomatic Multiple Myeloma according to the IMWG criteria, regardless of bone disease status

-Signed Informed Consent

-Age ≥ 18 years

-Remaining life expectancy ≥ 2 years

-Any concurrent anti-myeloma treatment are allowed

Exclusion criteria:

-Previous treatment with bisphosphonate within the last 6 months

-Severely reduced renal function (creatinine clearance <30 mL/min despite fluid replacement)

-Known concurrent malignancy, excluding skin cancer

-Known hypersensitivity to zoledronic acid

-Pregnant or lactating women

-Women of childbearing potential or men engaging in sexual activity with a woman of childbearing potential who refuse to use contraception (safe methods of contraception are considered to be: combined (estrogen and progestogen containing) hormonal contraception associated with inhibition of ovulation, progestogen-only hormonal contraception associated with inhibition of ovulation, intrauterine device (IUD), intrauterine hormone-releasing system ( IUS) bilateral tubal occlusion, vasectomy, and sexual abstinence. Contraception must be used until 56 days after the last infusion).

Criteria for randomisation (at year two):

-No severely reduced renal function (creatinine clearance <30 mL/min despite fluid replacement)

-No progressive bone disease diagnosed using bone imaging, less than or equal to three month prior to the randomization (year two)

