Bone imaging should be conducted using both conventional radiography and low-dose CT. Sites however may participate in the study without conducting both conventional radiography and low-dose CT. In this case, the chosen modality must be used consistently throughout the entire study period.

Fasting serum bone markers should be collected every fourth week (+/- 1 week) throughout this period. Serum samples do not need to be collected at the exact date of zoledronic acid infusion but can be collected up to two weeks prior to infusion; serum samples however must not be collected after zoledronic acid infusion. Measurements of creatinine and calcium may be conducted up till 2 weeks before the visit

QoL questionnaire QLQ-C30 and MY20 will be used every 3^rd^ month: after 27, 30, 33, 36, 39, 42, 45, and after 48 months. All time-points can be moved -2 weeks.

Infusion with zoledronic acid in the treatment arm should be given ever 4^th^ week (+/- 1 week). Infusion can be delayed for up to 2 months e.g. due to temporarily impaired renal function (meaning a three month pause between two infusion is allowed). If infusions cannot be given within this time period the patient will be excluded from the study.

For specific instructions concerning conventional radiography and low-dose CT, see appendix 2

For specific instructions concerning serum bone makers, see appendix 3

Amendment:

Patients who are included after 23-25 zoledronic acid infusions outside protocol will move directly to randomisation. The randomisation procedure will be stratified according to previous autologous stem cell treatment, presence or absence of bone disease at diagnosis, and previous treatment with bortezomib. Randomisation will take place at The Hematological Research Unit, Odense University Hospital, Denmark. For further details see appendix 6 (SOP for randomisation).

Acquiring source data (amendment):

Bone imaging must not be done more than two months prior to inclusion and should be done no more than one month after inclusion.

Fasting serum bone markers must be collected no more that 2 weeks after inclusion.

QoL questionnaire QLQ-C30 and MY20 should be completed no more that 2 weeks after inclusion.

Investigation according to local guideline for any pre-existing BON must be conducted before inclusion in the protocol amendment

Planned visits, year 2-4: (amendment)

No changes compared to original description.

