**1.8 Safety Considerations and Drug administration.**

The most clinically relevant side effects to zoledronic acid include impaired renal function, hypocalcaemia, and BON. Because of this, evaluation of renal function and supplementary intake of calcium +/- vitamin D should be conducted in accordance with local guidelines. During the study, serum creatinine and ionized calcium will be measured monthly and recorded in the CRF.

Risk of BON

Concerning BON, patients should receive a thorough dental examination prior to treatment initiation if possible, maximal dental hygiene should be maintained and conservative approaches should be applied if dental problem arises. Oral investigation will be conducted at least once a year in the first two years and every 3 months from year 2 to 4 by the treating physician in order to detect any cases of BON. All cases of BON will be recorded in the CRF. All cases of BON will be reported annually to the sponsor. In case of BON, it is up to the treating physician to decide if it is in the best interest of the patient to remain on bisphosphonate treatment or if treatment should be stopped, in which case the patient is excluded from the study.

In case dental problems arise, they shall if possible be treated conservatively. No data exists as to whether zoledronic acid should be withheld or continued if tooth extraction cannot be avoided. If the treating clinician finds in the best interest of the patient, infusion with zoledronic acid may be withheld up to one month prior to tooth extraction, and up to maximum three months after tooth extraction, thus allowing a four-month pause in total from zoledronic acid treatment. It is recommended however that the patients receive prophylactic antibiotic in case tooth extraction cannot be avoided [[12](#_ENREF_12)].

Risk of PBD

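### A history of jaw osteonecrosis on zoledronic acid bars randomisation on the amendment route but is not a criterion at the year-two randomisation on the original route

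*Protocol*

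**What the plan says.** Section 1.6 has two lists that decide who is randomised.

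- **Amendment route.** Patients treated with zoledronic acid outside trials go straight to randomisation. They are excluded if they "Developed BON during earlier zoledronic acid treatment". Section 1.7 adds a check: "Investigation according to local guideline for any pre-existing BON must be conducted before inclusion in the protocol amendment".
- **Original route.** Patients enter at diagnosis, receive two years of drug and must then meet the year-two criteria. These are adequate renal function, at least 12 infusions, and "No progressive bone disease diagnosed using bone imaging, less than or equal to three month prior to the randomization (year two"). BON is not mentioned there, nor in the original exclusion criteria.

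For BON arising during treatment, section 1.8 leaves the decision to the clinician: "In case of BON, it is up to the treating physician to decide if it is in the best interest of the patient" to stay on the drug or stop it, and stopping means leaving the study. The matching withdrawal ground in section 1.12 is "if the patient due to BON stops treatment with zoledronic acid". On oral examination, section 1.8 says "Oral investigation will be conducted at least once a year in the first two years and every 3 months from year 2 to 4".

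The incidence of BON from year 2 to year 4 is a secondary endpoint (section 1.5).

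**The concern.** Both routes lead to the same decision, to stop or to take two more years of drug. A history that is an absolute bar for one group is no criterion for the other. BON is the harm that the trial weighs against progressive bone disease (PBD) (sections 1.14 and 1.20), and section 1.14 presents the oral examinations as protection against overtreatment. On the original route a positive finding need not affect the one allocation that can add two years of exposure. No grade limit applies either, although section 1.9.1 treats persistent grade 2 and any grade 3 BON as serious adverse events.

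There is also a measurement side. The BON endpoint covers year 2 to year 4, and its definition requires exposed bone for more than 8 weeks without saying when it began. Recognised BON that started before randomisation is screened out on the amendment route but not on the original one.

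**Working it through.** The plan gives no figure to reproduce, so the main check sets the criteria side by side at randomisation.

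| Item | Original route, year two | Amendment route |
|---|---|---|
| Creatinine clearance below 30 mL/min | bars | bars |
| PBD on imaging within three months before randomisation | bars | bars |
| Minimum infusions | at least 12 | 23 to 25 |
| BON on earlier zoledronic acid | no criterion | bars |
| BON investigation required before entry to randomisation | not stated in the text shown | required |

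Take an original-route patient who develops BON in year 1 or 2 and whose physician continues the drug.

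1. Section 1.8 permits continuation, so the patient stays in the study.
2. The BON ground in section 1.12 does not apply, because the drug was not stopped.
3. With adequate renal function, no recent PBD and at least 12 infusions, every year-two criterion is met.
4. The patient can be randomised 1:1, possibly to two more years of drug. The same history on the amendment route means exclusion.

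**Scale, by assumption only.** Let q be the share of otherwise eligible original-route patients who reach year 2 with a BON history and still on drug. Let r be the share of the 286 randomised patients who come by that route. Patients affected = 286 × r × q.

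- q = 0: none.
- q = 1%, r = 1: 286 × 0.01 = 2.86, or 1.43 per arm.
- q = 1%, r = 0.5: 1.43.
- q = 3%, r = 1: 8.58, or 4.29 per arm.

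Neither q nor r is given in the protocol. The values only show what each percentage point would mean.

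**Effect on planned inclusions if these patients are not randomised.** The plan's own figure is 286 / 0.8 = 357.5, rounded up to 358, for a 20% loss before randomisation. Adding the exclusion, with all patients on the original route:

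- q = 1%: 286 / (0.8 × 0.99) = 361.1, so 362.
- q = 3%: 286 / (0.8 × 0.97) = 368.6, so 369.

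**The case against.** The strongest defence is that the routes differ for a reason. Amendment patients were treated outside the trial, so their BON status has to be established at entry. Original-route patients have been under trial observation: oral checks at least yearly, every BON case recorded in the CRF (section 1.9), and a decision to stop or continue whenever BON appears. A physician who thinks more drug is wrong stops it, and section 1.12 also allows removal for safety. A gap of more than three months between infusions excludes as well (four are allowed around a tooth extraction). Those left have BON, no such gap, and a physician who judged continuation to be right. That group may be empty.

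Most of this stands. It explains the extra investigation for amendment patients and limits the size of the problem. It does not explain why a known history is an absolute bar on one route and left to discretion on the other, at the same randomisation. PBD being the primary endpoint is a good reason to screen for it on both routes, but no reason to screen for BON on only one.

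A reader might go further and infer that original-route patients have no oral check at randomisation. The documents do not support that. The three-monthly schedule from year 2 can be read as starting at year 2. Appendix 1 (the flowchart) and Appendix 6 (the randomisation procedure), neither of which is shown, may also place a check there. All that can be said is that the text shown does not tie a check to randomisation.

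**Conclusion.** The inconsistency is real, and it is confined to the missing BON item in the year-two criteria. A patient with known BON who was kept on drug can be randomised to two more years on the original route, and recognised BON from before randomisation can enter the year 2 to 4 comparison on that route only.

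The number affected cannot be estimated from the protocol and may be zero; the scale figures rest wholly on an assumed share. A reader might also infer that the comparison of BON between arms is biased. That does not follow, because BON present before randomisation is expected to fall equally on both arms. If a share q of each arm were counted as cases regardless, the risk difference would become (1 − q) times its true value, a 1% shrinkage at q = 1%. The primary endpoint, time to PBD, is not touched. The weight is minor; the case for acting is that the change is cheap and concerns the trial's main harm.

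**What to change.** - Add the amendment's BON exclusion to the year-two randomisation criteria, so that one rule covers both routes.
- Do the oral investigation due around year 2 before randomisation, and record any exposed bone as a baseline finding even if it has lasted less than 8 weeks.
- Keep all randomised patients in the BON comparison, and report cases with exposed bone at baseline separately. Removing them would hide harm if further drug turned an early lesion into BON.

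The cost is one line in section 1.6 and the timing of an examination that is already planned. A few patients may not be randomised. Section 1.12 says "Patients will be included until this number is reached", which would allow replacement, but section 1.20 closes inclusion on 01.12.2020, so it is possible only until then. Under the assumed shares, planned inclusions rise from 358 to at most 362 (1%) or 369 (3%). No safety information from before year 2 is lost, since BON cases go into the CRF in any event. The new criterion bars established BON only; for a patient with a shorter-lived lesion at baseline, the decision stays with the physician.
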